### Study Schedule

All participants are required to complete electronic data entry forms at baseline and at 12, 26, and 52 weeks. Adherence, disease activity, QoL, PROs, IBD self-efficacy, and health care use will be measured at each time point during the 1-year study (Table 1). Demographic and clinical information will be collected at the baseline visit.

**Table 1 table1:** Schedule of events for the study.

Instrument	Category	Source	Baseline	Week 12	Week 26	Week 52
Demographics	Demographics	Patient	✓			
Clinical history	Clinical information	Provider or site	✓			
Medication adherence	Adherence	Patient		✓	✓	✓
MARS-5^a^	Adherence	Patient	✓	✓	✓	✓
Health care use	Health care use	Patient	✓	✓	✓	✓
Modified Harvey-Bradshaw Index	Disease activity: CD^b^	Patient	✓	✓	✓	✓
Simple Clinical Colitis Activity Index	Disease activity: UC^c^	Patient	✓	✓	✓	✓
C-reactive protein	Disease activity	Provider or site	✓	✓	✓	✓
Calprotectin	Disease activity	Provider or site	✓	✓	✓	✓
Simple endoscopic score: CD	Disease activity	Provider or site	✓	✓	✓	✓
Mayo Endoscopic Score	Disease activity	Provider or site	✓	✓	✓	✓
PROMIS^d^ Global Health Scale	Quality of life	Patient	✓	✓	✓	✓
PROMIS anxiety	Mental health	Patient	✓	✓	✓	✓
PROMIS depression	Mental health	Patient	✓	✓	✓	✓
PROMIS sleep disturbance	Mental health	Patient	✓	✓	✓	✓
PROMIS fatigue	Disease activity	Patient	✓	✓	✓	✓
PROMIS pain interference	Disease activity	Patient	✓	✓	✓	✓
PROMIS physical function	Frailty	Patient	✓	✓	✓	✓
IBD^e^ self-efficacy	Self-efficacy	Patient	✓	✓	✓	✓

^a^MARS-5: Medication Adherence Report Scale-5.

^b^CD: Crohn disease.

^c^UC: ulcerative colitis.

^d^PROMIS: Patient-Reported Outcome Measurement Information System.

^e^IBD: inflammatory bowel disease.

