### Outcomes and Outcome Measures

#### Overview

The outcome measures outlined in the following sections will be assessed at baseline and at 12, 26, and 52 weeks after initiating treatment. All outcome measures will be captured electronically and will not require a study or office visit.

The primary outcome of the proposed study will be the difference in mean MPR between the intervention and control groups during the 12-month study. The mean MPR will be calculated as follows:

MPR = number of days’ supply of medication obtained during observation period / total number of days in observation period.

If a participant discontinues therapy but initiates treatment with another eligible medication, the MPR will continue to be calculated. Any delay in initiating new treatment will be adjusted for the total number of days in the observation period (ie, if drug A is discontinued and drug B is started 2 weeks later, the observation period will be 365 – 14 = 351 days); for example, if a participant is prescribed oral mesalamine (1.2 g), 4 tablets daily, for 90 days (dispense 360) with 2 refills between months 6 and 12, the MPR would be 100%. Likewise, if a participant is prescribed ustekinumab 90 mg subcutaneous every 8 weeks (dispense 1 syringe) with 2 refills between months 6 and 12, the MPR would be 66%. Data on medication use will be self-reported by participants at each time point. However, we will randomly validate participant report via chart review of pharmacy data for 20% of the participants. Participants will report the date the medications of interest were filled as well as the number of days’ supply of medications filled. Self-reported adherence will be assessed with the Medication Adherence Report Scale-5 questionnaire (Table 2). Scores for each item are summed to give a total score, with higher scores indicating higher levels of reported adherence [33].

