The secondary outcome of the proposed study will be the difference in health care use between the intervention and control groups during the 12-month study. For health care use, we will use a composite end point, including counts of hospitalizations, urgent care or emergency room visits, IBD-related surgeries, telephone calls (primary care and IBD provider), endoscopic procedures, imaging examinations, and blood and stool testing. We will also assess new prescriptions for corticosteroids (prednisone and budesonide) at each time point during the study period. The total events will be adjusted per 100 patient years of follow-up because the 2 groups will be unequal in number. In addition, we will evaluate each outcome individually. The relatedness of hospitalization and urgent care or emergency room visits to IBD will be determined as well. Information will be obtained from patient self-report at each assessment. This approach has been validated in patients with IBD using a modification of the Canadian Community Health Survey [34]. However, we will validate participant self-report via chart review for 20% of the participants, randomly selected.

**Table 2 table2:** Medication Adherence Report Scale-5 questionnaire.

Item	Scoring				
	Always	Often	Sometimes	Rarely	Never
I forget to take my medication	1	2	3	4	5
I alter my medication dose	1	2	3	4	5
I stop taking my medication for a while	1	2	3	4	5
I decide to miss out a dose of my medication	1	2	3	4	5
I take less medication than instructed	1	2	3	4	5

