### Statistical Analyses

Baseline analyses will include tabulations of demographic and clinical variables of the study participants. Chi-square tests and 2-tailed *t* tests will be used to compare these groups to determine whether baseline differences exist. The distribution of each continuous variable will be inspected for outliers to determine whether a parametric or nonparametric approach should be applied. The Wilcoxon rank sum test will be used for any variable that does not meet the statistical assumptions of the *t* test. In addition, analyses will be conducted stratified by clinical site to determine whether the sites are comparable across the groups of interest. If differences are detected, these variables will be evaluated as potential confounders in the regression models.

For study aim 1, we will compare the mean MPR ratio between the intervention and standard of care groups using *t* tests. For study aim 2, we will compare differences in health care use between the groups using the Wilcoxon ranked sum test because we expect that the data will not be normally distributed.

For the secondary aims of clinical outcomes and health care use, dichotomized outcomes will be compared in a similar fashion with bivariate analyses. For health care use, the outcome will be investigated in quartiles of health care use, and specific outcomes of interest selected a priori will be investigated (eg, need for hospitalization for IBD, need for IBD surgery, and initiation of corticosteroids).

All analyses will be completed using intention-to-treat principles. Assuming 2 intervention participants for every 1 control, with adherence rates of 0.65 among controls and 0.9 in intervention participants and with a type I error rate of 0.05 and power of 0.9, we will need to enroll 123 participants: 82 (67%) in the intervention group and 41 (33%) controls. We may enroll more patients pending our initial recruitment and data capture.

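### Health care use is measured at baseline, but its named test uses neither that value nor the randomisation strata: an avoidable loss of precision, not bias

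*Protocol article*

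**What the plan says.** All places are in the Methods of the protocol article.

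- **Outcome.** Outcomes and Outcome Measures, Overview: "The secondary outcome of the proposed study will be the difference in health care use between the intervention and control groups during the 12-month study". It is a composite of event counts, with totals expressed per 100 patient-years.
- **Baseline value.** Study Schedule: "Adherence, disease activity, QoL, PROs, IBD self-efficacy, and health care use will be measured at each time point during the 1-year study". Table 1 ticks health care use at baseline and at all three follow-up times. The Overview agrees: "The outcome measures outlined in the following sections will be assessed at baseline and at 12, 26, and 52 weeks after initiating treatment".
- **Strata.** Study Conduct stratifies randomisation by study site and disease subtype, because these could affect response to the intervention. Prior health care use is not a stratification factor.
- **Named test.** Statistical Analyses: "For study aim 2, we will compare differences in health care use between the groups using the Wilcoxon ranked sum test". The only reason given is expected non-normality.
- **Other analyses of this outcome.** Statistical Analyses: "dichotomized outcomes will be compared in a similar fashion with bivariate analyses".
- **The only mention of adjustment.** After the baseline group comparisons and the site-stratified checks: "If differences are detected, these variables will be evaluated as potential confounders in the regression models". No regression model is described for either aim.

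**The concern.** People who used much care before entry may go on using much care. If so, part of the spread in 12-month use is predictable from a value the trial already holds. An unadjusted rank sum test leaves that part in the error term and does not correct for arms that differ by chance in prior use. Ignoring the stratification factors similarly leaves any site or subtype differences in the error term.

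Non-normality is a reason to use a rank or count method. It is not a reason to leave out the baseline value, because rank ANCOVA and count regression both accept covariates.

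With 41 controls planned and as much as 20% loss anticipated, precision is scarce. The endpoint also matters to the trial's message. In the team's previous telemedicine trial, described under Preliminary Work, health care use differed among the groups while disease activity and quality of life did not.

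**Working it through.** **1. The plan's own figure.** The article gives no sample size or power for health care use. Its 123 concerns adherence (0.65 vs 0.90, 2:1, alpha 0.05, power 0.90). Two-sided, without continuity correction, and with average proportion (0.65 + 2×0.90)/3 = 0.8167:

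n(control) = [1.960×√(1.5×0.8167×0.1833) + 1.282×√(0.65×0.35 + 0.90×0.10/2)]² / 0.25² = (0.929 + 0.669)² / 0.0625 ≈ 40.8, so 41.

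That gives 41 + 82 = 123, as stated. The figure is sound but does not bear on this endpoint, except to fix the arm sizes.

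**2. Analytic effect of adjustment.** Let ρ be the baseline to follow-up correlation (rank correlation for a rank ANCOVA). Adjustment multiplies the variance of the arm comparison by 1 − ρ², so

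adjusted power = Φ[(z(unadjusted power) + 1.96)/√(1 − ρ²) − 1.96].

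Example: from 80% at ρ = 0.5, (0.842 + 1.960)/0.866 − 1.960 = 1.275, and Φ(1.275) = 0.899. ρ is assumed throughout.

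| ρ | 1 − ρ² | Unadjusted N matching an adjusted 123 | From 60% | From 80% |
|---|---|---|---|---|
| 0.2 | 0.96 | 128 | 61.8% | 81.6% |
| 0.3 | 0.91 | 135 | 64.1% | 83.6% |
| 0.4 | 0.84 | 146 | 67.5% | 86.4% |
| 0.5 | 0.75 | 164 | 72.4% | 89.9% |

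**3. Simulation with baseline use as the only covariate.** Assumptions: gamma-Poisson counts, mean 10 per year before and after entry, frailty shape 2, rate ratio 0.65, 2,000 runs per setting, Wilcoxon versus Quade-type rank ANCOVA.

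| Arms | Rank correlation (approx.) | Wilcoxon | Adjusted | Gain (points) |
|---|---|---|---|---|
| 82/41 | 0.26 | 72.5% | 75.3% | 2.8 |
| 82/41 | 0.42 | 71.9% | 79.7% | 7.8 |
| 82/41 | 0.55 | 73.8% | 86.1% | 12.3 |
| 66/33 (20% loss) | 0.26 | 62.7% | 67.1% | 4.4 |
| 66/33 | 0.42 | 63.3% | 71.8% | 8.5 |
| 66/33 | 0.55 | 62.8% | 76.8% | 14.0 |

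A different set of counts (mean 8 per year, 3-month baseline window, rate ratio 0.7, frailty shape 4) moved power from 77.6% to 85.2% at rank correlation 0.43. Type I error was 4.5% to 6.1% in the first setup and 4.0% to 5.3% in the second, for both tests.

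**4. Simulation with the strata included (82/41).** Type I error stayed near 5%. Adjustment lost about 1 point at zero correlation. It gained about 0 to 3 points at rank correlations up to 0.3, 5 points at about 0.4 and 10 points at about 0.5.

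**5. Recall window.** The baseline window is not stated in the text shown. Rerunning the first model of step 3 at 82/41 with shorter windows:

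| Underlying frailty correlation | 12-month window | 3-month | 1-month |
|---|---|---|---|
| 0.50 | about 5 points (observed 0.39) | about 4 (0.31) | about 2 (0.22) |
| 0.65 | about 11 | about 8 | about 3 |

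A short window weakens the correlation and shrinks the gain.

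**6. Chance imbalance.** The standard error of a baseline difference between arms is √(1/41 + 1/82) = 0.191 SD, and 1.96 × 0.191 ≈ 0.37 SD. A difference in prior use of up to about 0.37 SD is therefore within the ordinary play of chance.

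**The case against.** The strongest defence is that nothing here is invalid. The Wilcoxon test holds its level under randomisation, the protocol claims no power for health care use, and covariates are commonly settled in an analysis plan that is not shown. All of the first two parts stands. The third does not dispose of the point: the article does not leave the method open but names a test that takes no covariate. The sentence on potential confounders does not repair this. It depends on what the baseline comparisons happen to show, does not name prior health care use, and refers to models specified for neither aim.

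The defence is also right that a strong correlation is assumed rather than shown. Everyone enrolled is starting a new therapy, so prior use may reflect the episode that led to the change. The composite counts telephone calls and tests that may follow the start of treatment, and intervention alerts themselves prompt staff contact.

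Four stronger readings are tempting but unsupported:

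- *The comparison is biased or its error rate inflated.* It is not. Chance imbalance is already covered by the 5% level.
- *A definite amount of power is lost.* No single figure can be given without the correlation and the recall window.
- *Adjustment would remove noise and imbalance.* It removes only the share that baseline explains, which is 9% of the variance at ρ = 0.3.
- *The team's earlier colitis trial shows the danger directly.* The imbalance reported there was in immune suppression use and quality of life, not in prior health care use. It shows that small trials can be unbalanced, no more.

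Nor should the word differences in the named test be read as change from baseline. The Overview defines the outcome as "the difference in health care use between the intervention and control groups during the 12-month study".

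**Conclusion.** The point holds as one of efficiency. The plan fixes an analysis of its named secondary outcome that ignores a baseline value it collects and the strata it randomises on. The test is valid. What is given up is precision and some protection against chance imbalance.

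At 82 versus 41, the power forgone is about 0 to 4 points at rank correlations up to 0.3, about 5 to 8 near 0.4 and about 10 near 0.5. These figures rest on assumed overdispersed counts, assumed effects and an assumed correlation. With a weak correlation or a short baseline window the gain is small. The case for change is that the downside is smaller still: about 1 point at zero correlation, with type I error unaffected.

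**What to change.** In Statistical Analyses, prespecify as the main analysis of health care use a comparison adjusted for baseline use, site and disease subtype, with these covariates fixed whatever any baseline test shows. Either form would serve:

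- **Rank ANCOVA (Quade type).** Regress ranked 12-month use on ranked baseline use plus site and subtype, and compare residuals between arms. This keeps the rank approach but yields a p-value rather than a rate.
- **Negative binomial regression with log follow-up time as offset.** This yields a rate ratio, matches the per-100-patient-years scale in the Overview, and allows for unequal follow-up under the anticipated loss. It was not part of the simulations above.

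With 5 sites and 2 subtypes, main effects need 4 + 1 = 5 terms. Keep the plain Wilcoxon test as a sensitivity analysis.

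The cost is a sentence or two of analysis text, settled before any comparison by arm, and no new data. The plan must also state a rule for missing baseline values and the recall window of the baseline questionnaire. A window that differs from the follow-up period weakens the gain but does not bias the randomised comparison.

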We then pursued a 12-month randomized clinical trial to assess the effectiveness of the UC HAT system compared with best available care (BAC). We modified the symptom diary and alert criteria to make them specific to UC and added action plans and electronic messaging for participants to communicate with the research team. Adults with UC from the University of Maryland and Veterans Affairs Hospital in Baltimore were randomized to self-testing with the UC HAT system weekly or BAC. All participants underwent visits at baseline and every 4 months. Disease activity was measured using the Seo index [18,19], disease-specific QoL was measured using the Inflammatory Bowel Disease Questionnaire [20], and medication adherence was measured using a medication adherence scale [21]. We randomized 47 patients, and 29 (62%) completed the study. After adjustment for baseline QoL scores, participants in the UC HAT arm had a strong trend toward decreased Seo index scores from baseline (mean –11.9, SD 6.6; *P*=.08). Furthermore, after adjustment for baseline disease knowledge, participants in the UC HAT arm had a significant increase in QoL scores from baseline (mean 12.5, SD 5.9; *P*=.04), whereas participants in the BAC arm had nonsignificant decreases in QoL scores from baseline (mean –3.8, SD 5.3; *P*=.47). The difference in change in QoL scores from baseline between the UC HAT and BAC arms at 12 months was significant. Self-reported adherence to medical therapy was low in both groups at baseline (BAC: 45% and UC HAT: 40%). Adherence rates increased in both groups but were not significantly different at any time point after baseline. Both arms had poor IBD knowledge at baseline, with improvement at the 12-month follow-up; however, there was not a significant difference between the UC HAT and BAC arms at the 12-month follow-up [22]. Our results suggested that the randomization process was inadequate because participants in the UC HAT arm had higher rates of immune suppression use and greater impairments in QoL than participants in the BAC arm. We suspect that the baseline differences in favor of the BAC arm impaired our ability to demonstrate a treatment effect of the UC HAT system. This hypothesis is supported by the findings of clinically important improvements in disease activity and QoL from the baseline to the 12-month visit in the UC HAT arm. Furthermore, after adjustment for baseline disease knowledge, a significant improvement in QoL was noted in the UC HAT participants.

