### Study Population

Patients will be recruited for this study from 5 clinical centers at the University of Maryland School of Medicine, University of Cincinnati School of Medicine, NYU Grossman School of Medicine, University of North Carolina School of Medicine, and Vanderbilt University School of Medicine.

Inclusion criteria will include (1) aged ≥18 years; (2) documented IBD based on usual diagnostic criteria, including clinical symptoms and findings from endoscopy, radiology studies, and histology [30]; (3) initiation of treatment with a new oral or subcutaneous treatment for IBD; (4) access to a smartphone with a reliable data plan or Wi-Fi access; and (5) ability to understand the protocol and provide informed consent in English. Exclusion criteria will include (1) inability to speak and read English or comply with the study protocol; (2) the presence of an ileostomy, colostomy, ileoanal pouch anastomosis, or ileorectal anastomosis; (3) initiation of oral corticosteroids only without concurrent use of an oral or subcutaneous maintenance therapy; (4) imminent surgery within the next 60 days; (5) history of short bowel syndrome; or (6) uncontrolled medical or psychiatric disease.

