#### Assessment of Disease Activity

To measure disease activity in participants with CD, we will assess a modified HBI without including the item on the presence of an abdominal mass (Table 3). HBI scores of <5, 5 to 7, 8 to 16, and >16 correlate with symptomatic remission, mildly active symptoms, moderately active symptoms, and severely active symptoms, respectively. A decrease in the HBI score of 3 or 4 correlates well with a symptomatic response [35].

In addition to calculating clinical remission and response using the aforementioned measures, we will create an outcome of steroid-free remission or response based on whether the patient was on concurrent steroids at the time of assessment. In patients with UC and indeterminate colitis, disease activity will be assessed with the SCCAI (Table 4). An SCCAI score of <3 has been shown to correlate with symptomatic remission, whereas a decrease of 2 points has been shown to correlate with a symptomatic response [36].

**Table 3 table3:** Modified Harvey-Bradshaw Index.

Item	Scoring
General well-being	Well: 0, fair: 1, poor: 2, terrible: 3
Abdominal pain	None: 0, mild: 1, moderate: 2, severe: 3
Number of liquid stools per day	Each liquid stool: 1
Arthralgia	Yes: 1, no: 0
Uveitis	Yes: 1, no: 0
Erythema nodosum	Yes: 1, no: 0
Aphthous ulcers	Yes: 1, no: 0
Pyoderma gangrenosum	Yes: 1, no: 0
Anal fissure	Yes: 1, no: 0
New fistula	Yes: 1, no: 0
Abscess	Yes: 1, no: 0

**Table 4 table4:** Simple Clinical Colitis Activity Index.

Item	Scoring				
	0	1	2	3	4
Bowel frequency (day)	1 to 3	4 to 6	7 to 9	>9	N/A^a^
Bowel frequency (night)	None	1 to 3	4 to 6	N/A	N/A
Urgency of defecation	None	Hurry	Immediately	Incontinence	N/A
Blood in stool	None	Trace	Occasionally frank	Usually frank	N/A
General well-being	Very well	Slightly below par	Poor	Very poor	Terrible
Aphthous ulcers	None	Present	N/A	N/A	N/A
Uveitis	None	Present	N/A	N/A	N/A
Erythema nodosum	None	Present	N/A	N/A	N/A
Arthralgia	None	Present	N/A	N/A	N/A

^a^N/A: not applicable.

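### For the clinical outcomes of aim 2 the only analysis named is a bivariate comparison of dichotomies; baseline adjustment hangs on baseline tests and unspecified models, and the Crohn response threshold is left open

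*Protocol article*

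**What the plan says.** Protocol article, Study Schedule: "Adherence, disease activity, QoL, PROs, IBD self-efficacy, and health care use will be measured at each time point during the 1-year study". Table 1 places the modified HBI (Crohn disease), the SCCAI (ulcerative colitis), the PROMIS scales and IBD self-efficacy at baseline and weeks 12, 26 and 52.

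Statistical Analyses: for clinical outcomes, "dichotomized outcomes will be compared in a similar fashion with bivariate analyses". The tests named for the other outcomes are the *t* test (MPR) and the Wilcoxon test (health care use). On baseline variables: "If differences are detected, these variables will be evaluated as potential confounders in the regression models". No such model is described.

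Assessment of Disease Activity: remission is HBI below 5 or SCCAI below 3. For response in Crohn disease, "A decrease in the HBI score of 3 or 4 correlates well with a symptomatic response"; for the SCCAI, "whereas a decrease of 2 points has been shown to correlate with a symptomatic response".

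Study Population: the treatment criterion is "initiation of treatment with a new oral or subcutaneous treatment for IBD". No criterion sets a minimum disease activity. Study Conduct: randomization is stratified by site and disease subtype, and participants and physicians are not blinded.

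IBD Home Automated Telemanagement, on the earlier randomized trial in ulcerative colitis: "We suspect that the baseline differences in favor of the BAC arm impaired our ability to demonstrate a treatment effect". The imbalances named there were in quality of life and use of immune suppression.

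**The concern.** Aim 2 asks whether the system changes clinical outcomes. A yes/no comparison at a cut-off discards most of what a graded score carries, and an unadjusted one also forgoes the precision that the entry score would give. Stratifying by site and subtype does not balance disease activity or quality of life, the latter being one of the imbalances the team suspects hurt its earlier trial.

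Adjusting only when a baseline test finds a difference is a weak remedy. With 82 and 41 participants such a test can miss an imbalance that matters, and the choice of covariates becomes data-driven.

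The response endpoint has two further problems:

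- Some participants may be unable to respond, which would dilute the response rate in both arms if they stay in the denominator.
- Two HBI thresholds in an unblinded trial leave room to choose after data are seen.

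**Working it through.** **1. The plan's own figure.** The article gives a sample size only for adherence. Per control, with allocation k = 2, rates 0.65 and 0.90, two-sided 0.05 and power 0.90:

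n = [1.960·√((1 + 1/k)·p̄q̄) + 1.2816·√(p₁q₁ + p₂q₂/k)]² / (p₂ − p₁)²

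p̄ = (0.65 + 2 × 0.90)/3 = 0.8167, so n = [1.960·√0.2246 + 1.2816·√0.2725]² / 0.0625 = 40.9. That rounds up to 41 controls and 82 intervention participants, 123 in total. The figure reproduces. It says nothing about power for clinical scores.

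**2. Numbers evaluable.** The 20% loss is the article's own upper figure: 82 × 0.8 ≈ 66 and 41 × 0.8 ≈ 33. HBI is scored only in Crohn disease. If the Crohn share matches the earlier telemedicine trial (236/348 = 67.8%; an assumption), 66 × 0.678 ≈ 45 and 33 × 0.678 ≈ 22. That leaves about 21 and 11 for the SCCAI.

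**3. Assumptions.** The article gives no SD, effect size or baseline–outcome correlation for any clinical score. I take a normal score, a difference of 0.5 SD at week 52, correlation ρ of 0.3 to 0.6, control success of 30% to 50%, and two-sided 0.05.

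**4. Formulas (normal approximation).**

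- Continuous score: power = Φ(0.5/√[(1 − ρ²)(1/n₁ + 1/n₂)] − 1.96), with ρ = 0 for the unadjusted comparison.
- Dichotomy: p_T = Φ(Φ⁻¹(p_C) + 0.5), so control success of 0.50, 0.40 or 0.30 becomes 0.691, 0.597 or 0.490. Power = Φ([p_T − p_C − 1.96·s₀]/s₁), with s₀ the pooled and s₁ the unpooled standard error.

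Example at 66 vs 33:

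- Unadjusted: 0.5/√0.04545 = 2.345, power 0.65.
- Adjusted at ρ = 0.6: 2.345/0.8 = 2.93, power 0.83.
- Dichotomy at p_C = 0.5: (0.1915 − 1.96 × 0.1031)/0.1040 = −0.10, power 0.46.

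| Evaluable | Dichotomized | Unadjusted score | Adjusted, ρ = 0.3 to 0.6 |
|---|---|---|---|
| 66 vs 33 (scales used in everyone) | 44–46% | 65% | 69–83% |
| 45 vs 22 (HBI, Crohn disease) | 31–33% | 48% | 52–67% |
| 21 vs 11 (SCCAI) | 17–19% | 27% | 29–39% |

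A *t*-based calculation lowers the continuous figures by one or two points in the smaller groups.

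**5. The same result as efficiency.** A cut of a normal score keeps φ(z)²/[p(1 − p)] of the information: 0.64 at a 50% cut and 0.58 at a 30% cut. Against a baseline-adjusted score, multiply by (1 − ρ²). At the 50% cut this gives 0.637 × 0.91 = 0.58 for ρ = 0.3 and 0.637 × 0.64 = 0.41 for ρ = 0.6.

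**6. Who can respond.** No score can fall below zero. A participant entering with HBI 0 to 2 cannot fall by 3 or by 4, and one entering at exactly 3 can respond under one threshold and not the other. A participant entering with SCCAI 0 or 1 cannot fall by 2. All of these are already in remission by the article's cut-offs, and nothing in the eligibility criteria keeps them out.

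**The case against.** The strongest reply is that this is a condensed article about secondary outcomes. The trial is sized on adherence, health care use is the named secondary outcome, and the choice of longitudinal model belongs in an analysis plan that is not shown. That stands as a limit on priority. It does not remove the point, because the article does name a method for clinical outcomes, and an analysis plan that followed it would inherit the weakness.

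Several stronger readings are tempting, and the document does not support them:

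- *Every scale will be dichotomized.* The sentence covers outcomes that are dichotomized. Cut-offs for remission and response are given for HBI and SCCAI. PROMIS has severity bands but no responder rule, self-efficacy is only a total score, and MARS-5 is a summed adherence measure rather than a clinical outcome.
- *Baseline is discarded altogether.* Response is itself a change from baseline.
- *Stratification is the only protection against imbalance.* The article also allows baseline variables that differ into regression models. That route is conditional and undefined, but it exists.
- *Imbalance sank the earlier trial.* The team only suspects that it impaired detection, and reports a significant quality-of-life gain after adjusting for baseline disease knowledge.
- *Low scorers are counted as non-responders.* No response denominator is stated.
- *The 66 vs 33 power figures describe disease activity.* They apply only to scales used in both diseases; HBI and SCCAI have far fewer participants.

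**Conclusion.** The point holds in a bounded form. For the clinical part of aim 2, the stated analysis is bivariate on dichotomized data, and adjustment rests on tests of baseline difference and models that are not described. Remission ignores entry score, response is out of reach for some eligible participants, and the Crohn threshold is not settled.

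On the illustration, moving from a dichotomy to a baseline-adjusted score raises power by about 23 to 39 points for scales used in everyone (46% to 69%, up to 44% to 83%) and by about 19 to 36 points for HBI (33% to 52%, up to 31% to 67%). The sizes rest on the assumed effect, correlation, normality and Crohn share. HBI and SCCAI are bounded sums with fixed cut-offs, so the true loss could differ. The ordering holds throughout the range shown. Even the better analysis leaves HBI and SCCAI with modest power, so results on them should be read as estimates with intervals. Priority is moderate.

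**What to change.** Before any outcome data are seen, state in the analysis plan:

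1. HBI (Crohn disease) and SCCAI (ulcerative colitis or indeterminate colitis) are analysed as continuous scores in a repeated-measures model using all follow-up visits, with arm, visit, arm-by-visit, baseline score and site. The week-52 adjusted difference is reported with its confidence interval.
2. PROMIS and self-efficacy scores are handled in the same way, with disease subtype added.
3. Adjustment is unconditional; the rule that depends on baseline tests is dropped for these outcomes.
4. Remission is kept as a supportive binary outcome in a model adjusted for baseline score.
5. Response is assessed only in participants outside the article's own remission range at entry (HBI 5 or more, SCCAI 3 or more), and one of the two HBI thresholds is named.

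The cost is wording only, since every measurement is already scheduled. The one real downside is a smaller denominator for response. With about 32 evaluable SCCAI participants over five sites, the plan should also say how sparse sites are handled.
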